| 1. Refuse to participate after enrollment                                                                                                                                                                                                                                                                                                                                                                                                                                                                                                                                                                                                                                                                                                                                         | 230                                                         |
| 2. No data due to lost to follow-up                                                                                                                                                                                                                                                                                                                                                                                                                                                                                                                                                                                                                                                                                                                                               | 231                                                         |
| 3. New allergy to vaginal micronized progesterone                                                                                                                                                                                                                                                                                                                                                                                                                                                                                                                                                                                                                                                                                                                                 | 232                                                         |
| 4. An exclusion criteria that was existed before recruitment but was discovered afterwards.                                                                                                                                                                                                                                                                                                                                                                                                                                                                                                                                                                                                                                                                                       | 233
234                                                  |
| Study design: Multicenter open label randomized controlled trial.                                                                                                                                                                                                                                                                                                                                                                                                                                                                                                                                                                                                                                                                                                          | 235                                                         |
| Number of estimated medical centers: 3                                                                                                                                                                                                                                                                                                                                                                                                                                                                                                                                                                                                                                                                                                                                            | 236                                                         |
| Screening and enrollment                                                                                                                                                                                                                                                                                                                                                                                                                                                                                                                                                                                                                                                                                                                                                   | 237                                                         |
| Women diagnosed with preterm labor arrested by a tocolytic therapy will be evaluated. All women who satisfy the inclusion/exclusion criteria will be offered admission to this study.                                                                                                                                                                                                                                                                                                                                                                                                                                                                                                                                                                                             | 238
239
240                                           |
| Treatments, study groups, and patient management                                                                                                                                                                                                                                                                                                                                                                                                                                                                                                                                                                                                                                                                                                                           | 241                                                         |
| Patients diagnosed with arrested pre-term labor will be invited to participate and receive vaginal micronized progesterone (Utrogestan– 200mg×2 PV(per vagina) per day) versus no treatment.                                                                                                                                                                                                                                                                                                                                                                                                                                                                                                                                                                                      | 242
243
244                                           |
| Preterm labor will be defined as at least three uterine contractions each lasting 30 seconds or more per 30 minutes confirmed by external tocography and presence of one of the following :                                                                                                                                                                                                                                                                                                                                                                                                                                                                                                                                                                                       | 245
246
247                                           |
| 1. Cervical length of 25 mm or less.                                                                                                                                                                                                                                                                                                                                                                                                                                                                                                                                                                                                                                                                                                                                              | 248                                                         |
| 2. Cervical dilatation of 1–4 cm accompanied by cervical effacement of at least 50%.                                                                                                                                                                                                                                                                                                                                                                                                                                                                                                                                                                                                                                                                                              | 249                                                         |
| The tocolytic treatment (first, second and third lines) will be determined by the attending physician at the time of admission and later on according to the departmental protocol. In addition, all patients will be screened for GBS (group B Streptococcus ) colonization if GBS status is unknown and urinary tract infections and treated appropriately. All patients will receive betamethasone for fetal lung maturity and appropriate GBS prophylaxis if those are indicated according to the departmental protocol. The tocolytic treatment which was successful in arresting the preterm labor will be continued for 48 hours. Arrest of preterm labor will be defined as 6 or fewer contractions per hour, intact membranes, and $\leq 4$ cm cervical dilation. | 250
251
252
253
254
255
256
257
258 |
| If the patient has an arrest of preterm labor, she will be asked to participate in this study. She will receive the first dose of the study medication at least 24 hours after initial treatment with tocolytic treatment and up to 3 days after finishing the tocolytic treatment, and then daily until 36+6 weeks or delivery (if occurs before 36.6 weeks).                                                                                                                                                                                                                                                                                                                                                                                                                    | 259
260
261
262                                    |

|                                                                                                                                                                                                                                                                                                                                                                                                                                                                                                                                                                                                                                                                                                                                                                                                                                         |                                                                    |
|-----------------------------------------------------------------------------------------------------------------------------------------------------------------------------------------------------------------------------------------------------------------------------------------------------------------------------------------------------------------------------------------------------------------------------------------------------------------------------------------------------------------------------------------------------------------------------------------------------------------------------------------------------------------------------------------------------------------------------------------------------------------------------------------------------------------------------------------|--------------------------------------------------------------------|

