**Abstract**

8

**Background:** Preterm labor is the leading cause of neonatal mortality and morbidity. Therefore, once preterm labor is diagnosed before 34 weeks of gestation, tocolytic therapy is initiated in an effort to prolong the pregnancy. Despite meticulous research for useful tocolytics, the medications that are available for this indication have been proven useful for only approximately two days, and searching for a more useful agent for labor arrest is imperative. It has been suggested that progesterone derivatives are useful in preventing preterm labor in women with cervical shortening or preterm labor in the past. However, the impact of progesterone has not been sufficiently tested for pregnancy prolongation after tocolytic therapy.

**Working hypothesis and aims:** Since progesterone derivatives are useful in preventing preterm labor in cases of risk factors or previous preterm labor, they will also show efficacy in pregnancy prolongation in women whose preterm labor was arrested following tocolytic treatment. The study aim is to evaluate the efficacy of vaginal progesterone for the prolongation of pregnancy after arrested pre-term labor.

**Methods:** Multicenter randomized controlled trial. Patients diagnosed with arrested pre-term labor following tocolytics at 24-34 gestational weeks will be randomly allocated to receive either vaginal micronized progesterone 400 mg/day (200 mg\*2/day) or no treatment. The primary outcomes are the mean number of days from enrollment to delivery and the rate of preterm delivery prior to 37 weeks of gestation. Secondary outcomes include need for additional tocolytic therapy, the rate of pregnancies prolonged for at least one week, neonatal complications, and admission to neonatal intensive care unit.

Assuming mean difference between the groups of 7 days  $\pm$  14 days a sample size of 64 women per group will be required (5% two-sided alpha, 80% power). This sample size is sufficient to detect a reduction from 50% to 25% in the rate of women who delivered prior to 37 weeks (5% two-sided alpha, 84% power). Considering 10% drop outs, 140 women will be required for this study (70 per group).

**Expected results:** Progesterone will be useful to prolong pregnancy after preterm labor was arrested with tocolytics.

**Importance:** This study has the potential to find a treatment to prevent preterm labor and thus to dramatically reduce neonatal morbidity and mortality.

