| Yet, the study methodology had potentially serious flaws; first, over 25% of                | 132 |
| participating women did not return the unused medication, and among those who did,          | 133 |

the authors stated that they could not be certain that they really administered it. 134  
 Second, the definition for threatened preterm birth included cervical length  $\leq 30$  mm 135  
 until 31 gestational weeks and/or positive qualitative fetal fibronectin test, which 136  
 serve more as screening markers for preterm labor than actual signs of threatened 137  
 preterm birth. Therefore studies with more strict inclusion criteria for preterm birth as 138  
 well as higher dose of progesterone should be performed. In the present study we 139  
 would like to investigate the effect of daily 400 mg vaginal micronized progesterone 140  
 for the prolongation of pregnancy after arrested pre-term labor. 141

142

**Study hypothesis:** Vaginal micronized progesterone will prolong the interval 143  
 between labor arrest with tocolytic therapy and the development of labor. 144

**Study outcomes** 145

**Primary Outcomes:** 146

1. The mean number of days from enrollment to delivery 147

2. The rate of preterm spontaneous delivery (defined as spontaneous labor or preterm 148  
 delivery following induction/cesarean section due to preterm premature rupture of 149  
 membranes prior to 37 weeks of gestation) 150

**Secondary Outcomes:** 151

*Obstetrics* 152

1. Number of days from recruitment to repeated preterm labor episode or 153  
 preterm premature rupture of membranes, up to 37 weeks of gestation 154

2. Pregnancy prolongation beyond one week 155

3. Need for repeated acute tocolysis 156

4. Number of hospitalizations and length of stay until 36.6 gestational weeks 157

5. The rate of preterm spontaneous labor (defined as spontaneous labor or 158  
 preterm premature rupture of membranes prior to 37 weeks of gestation) 159

160

161

|                                                                                                                                                                                                                                                                                                                                                                                                                |                                               |

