| • Nausea                                                                               | 304 |
| • Dizziness                                                                            | 305 |
| Severe adverse effects (e.g., anaphylaxis) will be reported to the Helsinki Committee. | 306 |
| Sample Size and statistics                                                      | 307 |
| Assuming mean difference between the groups of 7 days $\pm$ 14 days a sample size of   | 308 |
| 64 women per group will be required (5% two-sided alpha, 80% power). This sample       | 309 |
| size is sufficient to detect a reduction from 50% to 25% in the rate of women who      | 310 |
| delivered prior to 37 weeks (5% two-sided alpha, 84% power). Considering 10% drop      | 311 |
| outs, 140 women will be required for this study (70 per group).                        | 312 |
|                                                                                        | 313 |
| Patients' confidentiality                                                | 314 |
| Patients' personal information will be kept in sealed brown envelop separated from     | 315 |
| the CRF. Each patient will receive a code number written beside the patient name       | 316 |
| inside the aforementioned envelop. Only the patient's code will be written in the CRF  | 317 |
| form. All study data will be regarded in a locked closet inside a closed room.         | 318 |
|                                                                                        | 319 |

|                                                                                                                                                                                                                                                                                                                                 |                          |
|---------------------------------------------------------------------------------------------------------------------------------------------------------------------------------------------------------------------------------------------------------------------------------------------------------------------------------|--------------------------|

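### Two primary outcomes each carry the full two-sided 5% with no rule joining them: about 7–9% family-wise error if either suffices, about 70–75% joint power if both must succeed

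*Protocol*

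**What the plan says.** The abstract names two primary outcomes: "The primary outcomes are the mean number of days from enrollment to delivery and the rate of preterm delivery prior to 37 weeks" of gestation. The Study outcomes section lists two numbered items under one heading for primary outcomes. Item 1 is "The mean number of days from enrollment to delivery" and item 2 begins "The rate of preterm spontaneous delivery (defined as spontaneous labor or preterm".

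The sample-size text stands in the abstract and again under Sample Size and statistics. For the first outcome it reads "Assuming mean difference between the groups of 7 days" with a spread of 14 days, and concludes "64 women per group will be required (5% two-sided alpha, 80% power). This sample". It then says that the same number suffices for the second outcome, a "reduction from 50% to 25% in the rate of women who delivered prior to 37 weeks (5% two-sided alpha, 84% power". Each outcome thus has its own two-sided 5%.

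The protocol does not say whether one or both outcomes must be significant. It gives no testing order, no split of alpha and no multiplicity adjustment. The study hypothesis concerns only the interval to labor, but the protocol does not use it to rank the two outcomes.

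**The concern.** With two primary tests, the 5% and the power describe the trial's main claim only once a rule connects the tests to that claim. Without a rule, a result significant on one outcome alone could be called a success or a failure after the data are seen. The trial is open label with an untreated control group, and its expected conclusion is broad (progesterone helps to prolong pregnancy), so a rule fixed in advance matters more.

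The two obvious rules fail in different ways. If either outcome suffices, the chance of a false claim exceeds 5%. If both are needed, the chance of a true claim falls below the stated power.

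This is more than a detail left to the statistical analysis plan, because the protocol itself has assigned 5% to each outcome and derived its figures from that.

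**Working it through.** **Inputs.** From the sample-size text: difference 7 days, SD 14 days, 64 per group, rates 50% and 25%, two-sided alpha 0.05 for each outcome. From the eligibility criteria: tocolysis started between 24+0 and 34+0 weeks, a window of 70 days. The correlation between the two tests is not given, so a range is shown.

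**1. The protocol's own figures.**
- Days to delivery: standardized difference 7/14 = 0.5. A two-sample t-test at 0.05 needs 63.8, so 64 per group, with power 80.1%.
- Preterm rate: mean rate 0.375. SE under the null = √(2 × 0.375 × 0.625/64) = 0.0856. SE under the alternative = √((0.25 + 0.1875)/64) = 0.0827. Power = Φ((0.25 − 1.96 × 0.0856)/0.0827) = Φ(0.995) = 84.0%.

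Both figures reproduce with the full 0.05. At 0.025 each, the same formulas give 71.2% and 75.9%, so the stated n and power leave no room for an equal split. Under that split, 80% on the first outcome would need 78 per group by t-test.

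**2. If either outcome suffices.** Independent tests: 1 − 0.95² = 9.75%. For correlated tests, the bivariate normal probability that at least one |Z| exceeds 1.96 is:

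| Correlation | Family-wise error |
|---|---|
| 0 | 9.75% |
| 0.3 | 9.5% |
| 0.5 | 9.1% |
| 0.6 | 8.8% |
| 0.7 | 8.4% |
| 0.8 | 7.8% |
| 0.9 | 7.0% |

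Both outcomes come from the same delivery date, so they are dependent. To gauge how strongly, 20,000 null trials per scenario were simulated with 64 per group, normal latency with SD 14 days, 50% preterm, and preterm status derived from entry age plus latency. The SD of gestational age at entry is an assumption:

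| SD of entry age (days) | Correlation of latency and preterm status (absolute) | Family-wise error |
|---|---|---|
| 0 | 0.80 | 7.4% |
| 7 | 0.71 | 7.9% |
| 14 | 0.57 | 8.3% |
| 20 | 0.46 | 8.5% |

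Uniform entry over the 70-day window would have SD 70/√12 = 20.2 days. Repeated runs differ by a few tenths of a percentage point. Across runs the range was 7.0% to 8.9%, with the lowest values where entry age has no spread at all.

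**3. If both outcomes must succeed.** The error is at most 5%. Joint power from marginal powers of 80.1% and 84.0%, by bivariate normal:

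| Correlation | Joint power |
|---|---|
| 0 | 67% |
| 0.3 | 70% |
| 0.5 | 72% |
| 0.8 | 75% |

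**4. If the outcomes are tested in order, days first.** The second test is run only after the first succeeds, so the family-wise error stays at 5%. The first outcome keeps its 80%. The chance of claiming the second as well equals the joint power in step 3, because both tests must then be significant.

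**The case against.** The strongest reply is that the 5% levels and the sample size are not themselves wrong. A fixed sequence also tests each outcome at two-sided 5% with 64 per group, so only a sentence is missing, and an analysis plan that is not shown could supply it. The text also leans towards days to delivery. That outcome is listed first, it matches the hypothesis and it sets the sample size, while the preterm rate follows as a check on the same n.

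Part of this stands. Under a hierarchical reading the 5% and the 80% both hold, so it would be wrong to say that the stated figures fail under every reading. What does not stand is that the hierarchy is already there. Both outcomes are labelled primary, both carry full alpha, and no order is stated. An analysis plan could not split alpha equally without contradicting the protocol's n and power.

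Two stronger readings are tempting. A reader might infer that the trial's error rate is nearly double the nominal level, close to 10%. That needs independent outcomes, whereas these two share a delivery date. A reader might also infer that the protocol treats success on either outcome as enough. It does not say so, and the inflation is conditional on that rule.

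**Conclusion.** The point holds in conditional form. The protocol assigns two-sided 5% to each of two primary outcomes and gives no rule for combining them.

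- **Either suffices:** family-wise error is about 7–9%, and about 8–9% with realistic spread in entry age.
- **Both required:** error is controlled, and joint power is about 70–75% for correlations of 0.3 to 0.8.
- **Ordered, days first:** the 5% and the 80% stand, and the 84% describes only the second test taken alone.

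These figures rest on the protocol's own effect sizes and SD, on approximate normality, and on assumed correlations and entry-age spread. The protocol does not say which rule applies, and that choice should be fixed before outcome data are seen.

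**What to change.** State a fixed sequence under Sample Size and statistics, and match it in the abstract and the analysis plan:

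1. Test days from enrollment to delivery at two-sided 5%. It sets the sample size and matches the study hypothesis.
2. Test the preterm delivery rate at two-sided 5% only if the first test is significant. Otherwise report it descriptively with a confidence interval.
3. Describe the 84% as the power of the second test taken alone, since that test is reached only if the first succeeds.

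Before placing the second outcome in the sequence, reconcile its definition. The Study outcomes section restricts it to spontaneous preterm delivery, including delivery after preterm rupture of membranes, while the abstract and the sample-size text refer to delivery before 37 weeks. The 50% and 25% should then be confirmed for whichever event is kept.

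The cost is a few sentences. The sample size, the 5% level and the 80% for the first outcome are unchanged. The downside is that the preterm delivery rate cannot be claimed alone if the first test fails. If that is unacceptable, a Holm or Hochberg procedure is an alternative, but the power statement would have to be recalculated to match.
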